## Intervention

The Orygen HOPE aftercare is an evidence-informed, psychosocial program that provides intensive, person-centered, multi-disciplinary coordinated support which is tailored to the unique needs and circumstances of the individual young person using Relational Clinical Care (RCC) (see Table 2).

**Table 2 Tab2:** HOPE aftercare core RCC components

The core components of RCC		
Collaborative formulation, diagnosis, and psychoeducation		
Establishing and attending to the therapeutic relationship with young person and carers to enhance engagement and reduce barriers to treatment		
Family, carer, and system inclusive practice		
Young person and carer lived-experience peer support		
Brief intervention and time-limited episodic care		
Focus on the episode of care with a shared understanding of endings and supported transitions		
Collaborative care planning, including:		
a) Identification of co-occurring difficulties contributing to the acute presentation b) Goal setting c) Shared decision making and formulated treatment planning.		
Consistency and containment within the HOPE team via supervision and reflective clinical discussions.		

Young people referred to the Orygen HOPE aftercare are contacted within 24-hours of hospital/ED discharge; in-person assessment is arranged within 72-hours of the initial referral, and treatment is provided for up to three months. The RCC model positions the young person as the leader of the care team, and the multidisciplinary team delivers holistic support across psychological, family, psychosocial, and physical domains. The main feature of the HOPE service is collaborative work with the young person’s support system (family/carers, educational/vocational, healthcare, and community support providers) to understand, respond to and meet the wellbeing needs of the young person.

Young people referred to the Orygen HOPE aftercare will receive an assessment and treatment under the care of the Orygen HOPE multidisciplinary team. This consists of a consultant psychiatrist, psychiatric registrar, and allied health staff (clinical psychologist, psychologists, social workers, occupational therapists) providing clinical services. Youth peer workers and family peer workers are employed to provide additional support services. Orygen HOPE aftercare is governed directly by a lead consultant psychiatrist and team coordinator and sits within the broader governance structures of Orygen clinical specialist programs.

### Participants

#### Young people and carers

All young people (aged 12–25) who receive care from the Orygen HOPE aftercare will be invited to participate in the evaluation. Recruitment of participants will be facilitated by the Orygen HOPE clinical team. Following admission to Orygen HOPE aftercare, Orygen HOPE clients are presented at the clinical team meetings for discussion and allocation. A research team member will attend these meetings to be informed about the admission of new clients and to determine when to approach potential participants. Family members, support persons, and carers will also be invited to participate. To be eligible for the service, young people must meet the following criteria:

▪ Age between 12 and 25 years.▪ Presented to EDs within western and north–western metropolitan Melbourne following suicide attempt, or an episode of severe self-harm and/or significant levels of suicidal ideation.

Young people will be excluded from the service and referred to other appropriate services (e.g., other Orygen clinical services), if they present with any of the following criteria:

▪ Currently engaged in case management. ▪ Require acute care (will be initially managed by Orygen Acute).▪ Under a compulsory treatment order.▪ Present with psychotic symptoms or symptoms of hypomania or mania.▪ Have a complexity of mental health and psychosocial needs indicating a need for longer term case management or intensive care.

#### Service providers

All service providers involved in intake or delivery of the HOPE service will be invited to participate. This will include service coordinators, clinical leaders, clinicians, consultant psychiatrist, psychiatric registrar, youth peer support workers, family support workers, and Orygen’s intake assessors.

### Sample size and power

Based on a similar aftercare service developed for adults [22], we expect to detect a medium effect size of suicide ideation frequency reduction at the follow-up time point. To detect this effect, and assuming a correlation between baseline and follow-up measures of 0.5 and a drop-out rate of 30%, a sample of 184 young people will be needed.

### Data collection

To facilitate the evaluation, a range of data collection strategies and sources will be used, including electronic hospital records, self-report data, and surveillance and monitoring data (see Table 1).

Epidemiological data on rates of self-harm and suicidal ideation presentations across the catchment area will be obtained from routinely collected data extracted from electronic patient medical records. These data will be collected every six months throughout the life of the project and will provide information relevant to patients’ demographic characteristics, hospital presentations, referral sources, clinical descriptors, and assessments.

Patient-reported data will include data collected directly from young people and carers/parents/family members. Young people and family members will be recruited and consented to participation by the research team at the beginning of the young person’s treatment episode. Young people will provide quantitative survey responses at Time 1 (Baseline: at intake into treatment), Time 2 (Posttreatment: at discharge from treatment), and Time 3 (Follow-up: 3-months post–discharge from treatment). Family members/carers will provide quantitative survey responses at Time 1 and Time 2. Semi-structured interviews will be undertaken following completion of treatment with a select group of young people and family members/carers (*N* = 6–12 participants in each group). Interviews will be conducted in person or via video conference. The interviews will be conducted in Year 2 and Year 4 of this evaluation, allowing the service an opportunity to mature.

Service provider reported data will be collected via self-report surveys, individual semi-structured interviews, and group discussion via workshops, which will be undertaken annually. Specifically, surveys and interviews will be used to assess barriers and facilitators of the implementation across the five years. Workshops will be scheduled annually with the whole group of service providers and facilitated by the research team. The workshop discussion allows for appraisal of service strengths and weaknesses, and identification/prioritization of areas that need improvement. Using this methodology, providers identify the changes individually (via surveys) and then discuss responses in a participatory workshop to identify what needs to be improved to sustain the service.

Surveillance data will be collected from the Orygen’s Self-Harm Monitoring System for Victoria [28]. This database has been collecting information pertaining to self-harm and suicide ideation-related presentations across all major public EDs in Melbourne, Victoria.

### Measures

Demographic data (e.g., date of birth, gender, sex assigned at birth, country of birth) will be collected from participating young people and family members via surveys and from hospital-based records. Provider characteristics will be collected from providers via surveys, and will include HOPE aftercare role, time in role, total years’ experience in working with young people at risk of suicide, formal suicide-specific training received, and perception of training adequacy.

#### Primary outcome

*Suicidal ideation* will be measured using the Suicidal Ideation Attributes Scale (SIDAS; [29]). The SIDAS consists of five items (rated 0–10) each targeting an attribute of suicidal thoughts over the past month: frequency, controllability, closeness to attempt, level of distress associated with the thoughts, and impact on daily functioning. The SIDAS has demonstrated strong internal consistency and good convergent validity in a large online sample of Australian adults, including young people aged 18 and above [29].

#### Secondary outcomes

*Suicide attempts* will be assessed using four items from the United States Centers for Disease Control and Prevention’s National Youth Risk Behavior Survey (YRBS; [30]) assessing frequency and severity of suicide attempts over the past month. The YRBS displays appropriate psychometric properties for use with young people aged 13 to 18, including test–retest reliability [30].

*Self-harm* will be assessed using purpose-developed questions assessing type and frequency of self-harm events in the past month (e.g., “Have you ever engaged in an act of self-harm (with or without suicidal intent)? If yes, have you engaged in this behavior in the last month?”).

*Depressive symptoms* will be assessed using the 9-item Patient Health Questionnaire–9 (PHQ–9; [31]). The PHQ–9 focuses on severity of symptoms experienced over the past two weeks, with items rated on a 4-point Likert scale. It has established reliability and validity in acute and primary care [31], including young people [32, 33].

*Anxiety symptoms* will be assessed using the 7-item Generalized Anxiety Disorder Scale (GAD–7; [34]). The GAD–7 focuses on the frequency of symptoms experienced over the past two weeks, with items rated on a 4-point Likert scale. The GAD–7 has established reliability and validity in acute and primary care [31], including young people [35, 36].

*Psychological distress* will be assessed using the 10-item Kessler Psychological Distress Scale (K10; [37]). The K10 assesses generalized psychological distress experienced over the preceding 30 days. Items are rated on a 5-point Likert scale. The K10 has established reliability and validity across a variety of samples [37], including the Australian general population [38] and Australian adolescents [39].

*Mental health resource use* will be assessed using items adapted from the Young Mind Matters Service Use Questionnaire [40], referred to as the Resource Use Questionnaire (RUQ) for the purposes of the proposed study. These items assess relevant resource use (e.g., mental health services, ED attendance).

*Quality of life* will be assessed using the Child Health Utility–9D (CHU-9D) measure [41, 42]. The CHU–9D is a generic preference-based instrument designed to assess quality of life and facilitate economic evaluation of preventative and healthcare treatment programs aimed at young people. The CHU–9D has demonstrated practicality, face, and construct validity within a sample of Australian adolescents [43].

*The acceptability*,* appropriateness and feasibility* of the HOPE service will be measured using the Acceptability, Appropriateness, and Feasibility Measures (AAF) [44]. Items are rated on a 5-point Likert scale and assess the extent to which a given intervention is perceived as acceptable, suitable, and capable of being successfully implemented. The AAF has demonstrated appropriate psychometric properties [44].

Young people and their family members’/carers’ *satisfaction with the service* will be measured using routinely collected survey responses that gather information on domains including the degree to which service users feel their autonomy and values were respected, and their needs were supported during their episode of care.

*Treatment completion* including frequency, duration and components delivered during each individual episode of care, plus referral options provided following aftercare, will be collected via purpose-developed questions reported by providers via a short end-of-treatment form.

*Parental self-efficacy*, or confidence, around ability to engage in activities to support the young person in navigating a suicidal crisis will be measured using the 9-item Parental Self-Efficacy Scale (PSS; [45]). Items are rated on an 11-point scale. The PSS has reported good internal consistency [45].

*Provider knowledge and self-efficacy* will be assessed using purpose-developed questions based on previous program evaluations of suicide prevention (e.g., Zero Suicide) [46]. These questions will provide an overview of provider characteristics relevant to screening and assessing individuals for suicide risk (e.g., “I am comfortable screening individuals for suicide risk”), and providing appropriate care (e.g., “I am comfortable providing care to individuals who have been identified as being at elevated risk for suicide”), rated on a 5-point scale.

*Provider attitudes* will be assessed using the 14-item Attitudes to Suicide Prevention Scale (ASP; [47]). Items are rated on a 5-point scale. The ASP has demonstrated adequate reliability and internal consistency [47].

*Implementation moderators* will be measured using the Consolidated Framework for Implementation Research (CFIR) [48] Inner Setting measures (CFIR–IS; [49]). The CFIR–IS assesses culture overall, culture stress, culture effort, implementation climate, learning climate, leadership engagement, and available resources. The CFIR–IS has demonstrated appropriate psychometric properties [49].

*Implementation leadership* will be measured using the 12-item Implementation Leadership Scale (ILS) [50] supervisor and staff versions. The ILS comprises four subscales representing proactive, knowledgeable, supportive, and perseverant leadership. It has evidenced excellent internal consistency, as well as convergent and discriminant validity [50].

*Program sustainability* will be assessed using the 29-item Program Sustainability Index (PSI) [51]. The PSI assesses six elements: leadership competence, effective collaboration, understanding the community, demonstrating program results, strategic funding, staff involvement and integration, and program responsivity. The PSI has demonstrated acceptable internal consistency and validity [51].

The *Victorian Self-Harm Monitoring System* [28] will provide data regarding young people’s (12–25 years) presentations to EDs in the catchment area (north–west region of Melbourne) for the period between 1 January 2012 and 31 December 2026 (i.e., since the start of monitoring until the end of the evaluation). Data extracted will capture and compare hospital presentation trends across the specific time-period prior to HOPE service commencement (from 1 January 2012 to 31 December 2021) and following HOPE service commencement (from 1 January 2022 to 31 December 2026). Specifically, data extracted will utilize demographic descriptions (e.g., age, gender, postcode), rates of presentations for self-harm, clinical, and treatment characteristics (e.g., self-harm method, length of stay, discharge information, mental health referral).

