### Presentation rates

Many at-risk young people present to emergency departments (EDs) in crisis, following severe self-harm and/or a suicidal attempt [9]. In Australia, the hospital presentation rates are highest among young people aged 15–19 years (389 per 100,000 population) [10]. The rates of intentional self-harm hospitalization are steadily increasing [11]. The highest hospitalization rates are reported for females aged 15–19 and they have increased from 374 hospitalizations per 100,000 in 2008–09 to 637 hospitalizations per 100,000 in 2021–22 [10].

The risk of further suicide attempt/s is greatest immediately following discharge from the ED after a suicide attempt [7, 12] and remains high for up to 12 months following the attempt [12, 13]. Modelling studies with Australian data estimate that delivering better care at this time would reduce the numbers of self-harm hospitalizations and suicide deaths by 5.65% (95% CI, 4.87 − 6.42%) and 5.45% (4.68 − 6.22%), respectively [14]. This would mean ~ 1,616 fewer hospitalizations and ~ 33 fewer suicide deaths in Australia every year [15] .

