#### Economic evaluation

The economic evaluation will assess cost-effectiveness of the service or the value for money credentials using data described in the previous section. The long-term cost-effectiveness of the service will be determined using an economic evaluation suicide prevention model [53], which adopts a longer-term time horizon and estimates the reduction in suicide deaths using suicide attempts as a surrogate outcome.

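### The baseline attempt and self-harm items will usually count the event that made the participant eligible, so the uncontrolled pre-post contrast shows a fall even if HOPE has no effect

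*Protocol article*

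**What the plan says.** All references are to the protocol article.

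- **Recall window.** Under *Secondary outcomes*, attempts are measured with four survey items "assessing frequency and severity of suicide attempts over the past month", and self-harm with "purpose-developed questions assessing type and frequency of self-harm events in the past month". The sample self-harm question covers acts with or without suicidal intent.
- **Survey times.** *Data collection* sets "Time 1 (Baseline: at intake into treatment), Time 2 (Posttreatment: at discharge from treatment") and "Time 3 (Follow-up: 3-months post" discharge).
- **Entry.** *Young people and carers* admits those who presented to an emergency department "following suicide attempt, or an episode of severe self-harm and/or significant levels of suicidal ideation".
- **Timing of care.** *Intervention* has first contact within 24 hours of hospital discharge, in-person assessment within 72 hours of referral, and treatment for up to three months.
- **Success and analysis.** The effectiveness row of Table 1 defines success as a significant reduction from baseline to post-treatment, and names self-harm and attempts. *Quantitative analyses* repeats the primary outcome's change-over-time analysis for both.
- **Control.** The historical comparison uses emergency department surveillance data only. The survey outcomes have no comparison group.

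**The concern.** For someone who enters after an attempt or self-harm, the entry criterion and the baseline outcome are the same event. Assessment follows the presentation by days, so a past-month question at intake will normally pick that event up. Nothing selects for an event in the windows before discharge or follow-up. Baseline is raised by the way people enter the service, and the raised value is then the reference for the success criterion. This is more direct than ordinary regression to the mean, because the selecting event is itself counted in the outcome.

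A second, separate matter is coverage. Each later survey asks about one month only, while the gaps between surveys can be three months. Events in the uncovered months are lost unless they reach hospital. Table 1 also uses suicide attempt as a safety measure, drawn from the young person's survey and hospital records, so an attempt in an uncovered month that never reaches hospital escapes both sources.

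At stake is whether a positive result on two outcomes named in the effectiveness criterion could be told apart from no effect.

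**Working it through.** The article gives no expected rates for attempts or self-harm, so there is no stated figure to reproduce on this point. Its sample size (184, with 30% drop-out) was set for ideation. It is used here only for the number of completers: 184 × 0.70 = 128.8, about 129.

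**1. Fall expected with no effect of HOPE**

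Let *q* be the share of participants with an index attempt or self-harm event inside the intake window, and *r* the constant monthly background probability of an event. The article gives neither; both are assumptions.

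- Baseline prevalence: B = q + (1 − q)r
- Later prevalence: r
- Relative fall: 1 − r/B

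Worked case, q = 0.50 and r = 0.05: B = 0.50 + 0.50 × 0.05 = 0.525. Prevalence goes from 52.5% to 5%, a relative fall of 1 − 0.05/0.525 = 90%.

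The last column gives the share of 4,000 simulated data sets in which a McNemar-type test with 129 completers (|z| > 1.96) declares a fall. Background events at the two times are drawn independently.

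| q | r | Baseline | Later | Relative fall | Declared a fall |
|---|---|---|---|---|---|
| 0.25 | 0.05 | 28.7% | 5% | 83% | 99.9% |
| 0.25 | 0.20 | 40% | 20% | 50% | 94% |
| 0.50 | 0.20 | 60% | 20% | 67% | 100% |
| 0.75 | 0.10 | 77.5% | 10% | 87% | 100% |
| 1.00 | 0.02 | 100% | 2% | 98% | 100% |
| 0.25 | 0.40 | 55% | 40% | 27% | 68% |
| 0.10 | 0.40 | 46% | 40% | 13% | 16% |
| 0.10 | 0.02 | 11.8% | 2% | 83% | 91% |
| 0 | any of 0.02-0.40 | r | r | 0% | 2-3% |

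- For q from 0.25 to 1 and r from 0.02 to 0.20, the fall is 50-98% and is declared in at least 94% of simulations.
- With r = 0.40, conceivable for self-harm, the fall is 27-60% for the same q.
- With q = 0.10, the fall is 13-83% and is declared in 16-91% of simulations.
- With the index event excluded (q = 0), the artificial fall disappears.

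**2. Follow-up time not asked about**

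For an episode of L months (L from 1 to 3), the time from intake to the last survey is L + 3 months, of which two are covered. The share missed is (L + 1)/(L + 3).

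- L = 1: 2/4 = 50%
- L = 2: 3/5 = 60%
- L = 3: 4/6 = 67%

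Between discharge and follow-up it is always 2/3. In episodes longer than one month, the uncovered time includes the start of care. *Presentation rates* says "The risk of further suicide attempt/s is greatest immediately following discharge from the ED after a suicide attempt". With a three-month episode, the two windows capture 2/6 = 33% of events at constant risk, 23% if risk halves every two months and 14% if it halves monthly (assumed decay rates).

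**3. Does the uncovered time create the fall?**

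All three windows are one month long. In the model above, constant *r* with q = 0 gives no fall, whatever happens in the gaps. The artificial fall in step 1 therefore comes from selection on the index event.

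**The case against.** - **Ideation-only entry is allowed.** These participants carry no index event, and the index share is not given. This stands: it governs the size of the artefact and makes it modest at the low end. It does not reverse the direction.
- **The 24-hour and 72-hour limits govern clinical contact, not the research survey.** The research approach follows admission and team allocation, and some young people are first managed by the acute team. So *usually* is right and *always* is not. If 30% of index events fell outside the window, the worked case would have q = 0.35 and B = 0.35 + 0.65 × 0.05 = 38.25%, still a fall of 1 − 0.05/0.3825 = 87%.
- **Other evidence on behaviour exists.** These are secondary outcomes; the primary is ideation. The surveillance analysis has a historical control and recurrent-event models, and hospital records feed the safety assessment. This stands for events that reach hospital, but does not repair the survey contrast.
- **The article is condensed.** A fuller document may separate the index event. But the recall window, survey times and success criterion are fixed here, and no analysis can recover months that the questionnaire did not ask about.

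Two stronger readings are tempting and not supported. A reader might infer that the uncovered months also produce the fall. They do not at constant risk. If risk declines naturally, a fall would be ordinary single-arm confounding by time, which full coverage would not remove. A reader might also infer that these survey items are the attempts in the long-term economic model, which "estimates the reduction in suicide deaths using suicide attempts as a surrogate outcome". No passage says so. The measures section on economic evaluation says that user surveys inform the evaluation, but names the surveillance system for attempt rates. The cost-effectiveness row of Table 1 lists hospital re-presentation, resource use and quality of life, not the attempt items.

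**Conclusion.** The point holds for the attempt and self-harm survey outcomes. As written, the baseline count will usually include the qualifying event for attempt and self-harm entrants. A significant pre-post reduction on these outcomes would then not distinguish an effective service from an ineffective one.

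The expected fall with no effect is about 50-98% for index shares of 25-100% and background monthly probabilities of 2-20%. It is smaller, down to 13% in the settings tried, if the index share is near 10% or background self-harm is frequent. These sizes rest on assumed shares and rates, a constant background risk, and a simple paired test in place of the planned models.

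The coverage gap of 50-67% of follow-up time (67% for three-month episodes) is a separate loss of efficacy and safety information on events that do not reach hospital. It is not a cause of the fall.

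**What to change.** 1. **Intake survey.** Record the index event separately (attempt, self-harm, ideation only) with its date, and ask about other events in the month before it.
2. **Analysis.** Exclude the index event from every pre-post contrast on attempts and self-harm, and report results by index type.
3. **Discharge and follow-up surveys.** Add a question on events since the last survey, with number and approximate dates, analysed as a rate per person-time because the recall periods differ. Keep the past-month items for continuity and for the equal-window comparison.
4. **Participants already surveyed without this separation.** Present their attempt and self-harm change as descriptive, not as evidence of effect. Subtracting index events through hospital records may not be possible, since *Data storage* says that identifiers are removed and the researchers cannot re-identify the data.

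The cost is several reworded or added items (attempts alone use four), an ethics amendment, some extra recall error over up to three months, and a break with data already collected. The change removes the artefact from counting the index event. It does not supply a control group, so natural improvement over time would still be part of any observed change.
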